## Methods/design

### Objective of the study

The overall objective of this prospective randomized clinical trial with observer-blinded analysis is to assess the outcome of GO in patients with moderate-to-severe GO who receive early Tx after their first relapse of GO or in which GO stays the same following the initial decrease in their ATD therapy after 4–6 months.

The main outcome variables investigated include: muscle index (MI) measurements via ultrasound before randomization and 1 year after the conducted therapy, as well as thyroid antibody levels, measured at each follow-up appointment. Additional outcome variables such as CAScore/NOSPECS score (calculated at each appointment), superonasal index (SNI) measurements via ultrasound and quality of life score (both obtained before randomization and 1 year after the conducted therapy) will be analyzed. See Tables 4 and 5.

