### Statistical analysis

The data will be analyzed according to the intention-to-treat principle. This means, that for patients with missing MI values at follow-up measurements a conservative value will be imputed. If patients have a SNI >  7 during follow-up, which requires additional treatment, later MI values will be estimated using last value carried forward. The primary and continuous secondary endpoints will be analyzed using repeated measures analysis of covariance, using the randomization group as factor and the baseline values of MI as covariate. The contrast of main interest is the difference between groups in the means computed over all post-randomization measurements. MI and SNI will be obtained before randomization and 1 year after the conducted therapy. Quality of life questionnaire will also be obtained before randomization and after 1 year of follow-up. Further binary secondary endpoints will be analyzed by Mantel-Haenszel tests stratified for the clinical MI grading at baseline. All secondary endpoints will be analyzed at the specified time points (see Tables 4 and 5) and reported and thus no correction for multiple testing is done. Any analyses that will be conducted, but which are not mentioned in the study protocol, will be interpreted as explorative. A statistical analysis plan detailing all statistical computations will be completed prior to the lock of the database. Values are given as *p* values and odds ratio (95% confidence interval); *p* values < 0.05 are considered statistically significant. Analysis of data will be performed using SPSS (Statistical Package for Social Sciences, Chicago, IL, USA) v21 for Windows.

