## Discussion

This clinical trial is a single-center, prospective randomized trial designed to assess which therapy method provides the better outcome in patients with moderate-to-severe GO. Since moderate-to-severe GO can be debilitating, it is essential to find a treatment method that provides the optimum therapy and best quality of life. In addition, we hope to establish a standard glucocorticoid scheme before and after Tx, given that there is, to date, no such consensus in patients with moderate-to-severe GO.

There are several advantages and disadvantages to a single-center study. Some advantages to our study center are that it is conducted in a teaching hospital with a high volume of patients and all patients are treated with the same high standard. Given that our university hospital is the largest specialized center for GO within Austria, the majority of patients are sent to us. In single-center trials, the clinical investigators are continuously involved and communication is simplified (one set team is working together on this trial with specific contact persons from each clinical unit). Also, there is reduced variability regarding trial conduct and data collection. Some disadvantages include possible recruitment issues, thus resulting in failure to demonstrate a treatment difference when one is present (type II error). In order to overcome recruitment issues, we will present the clinical trials at other hospitals and at medical conferences within Austria to secure a high recruitment rate. Given that Graves’ patients with moderate-to-severe GO should only be treated in specialized centers due to the debilitating side-effects it can cause, generalizability to other settings should not be an issue.

As has been previously mentioned and demonstrated in various studies, the experts have not been able to come to a consensus on the treatment of Graves’ disease and GO, mainly due to the individuality of the disease in each patient. In addition, the usefulness of total thyroid ablation (TTA) has yet to be confirmed by long-term randomized controlled trials (RCTs). The follow-up periods in previous studies have been too short and were not standardized. Therefore, our study will perform a follow-up in each patient at 8, 16, 32 and 52 weeks after their treatment. This will allow for an assessment of the medium- to long-term effects follow surgery or continuation of ATD.

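### Intention-to-treat is spelled out only for MI, so antibody level would lose every patient with one missed sample if the named repeated measures ANCOVA is fitted in its classical form

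*Protocol article*

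**What the plan says.** All of the following is in the protocol article.

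- **Principle** (Statistical analysis): "The data will be analyzed according to the intention-to-treat principle". The next sentence explains what this means: "for patients with missing MI values at follow-up measurements a conservative value will be imputed".
- **Second missing-value rule** (same section): after an SNI above 7 that needs additional treatment, "later MI values will be estimated using last value carried forward". This also concerns MI only.
- **Model** (same section): "The primary and continuous secondary endpoints will be analyzed using repeated measures analysis of covariance", with randomization group as factor and baseline MI as covariate. SPSS v21 is named, but no procedure within it.
- **Contrast** (same section): "The contrast of main interest is the difference between groups in the means computed over all post-randomization measurements".
- **Antibody level** (Objective of the study): the main outcome variables are MI and "thyroid antibody levels, measured at each follow-up appointment". The Discussion gives the timing: "our study will perform a follow-up in each patient at 8, 16, 32 and 52 weeks after their treatment". Table 5 has a blood test at all four follow-ups.
- **Other endpoints** (Table 5): CAScore and NOSPECS at three follow-ups; ultrasound (MI and SNI) and quality of life at 1 year only.
- **Later detail** (Statistical analysis): a statistical analysis plan is to be completed before database lock. It is not at hand.

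**The concern.** The plan makes a general intention-to-treat claim and then gives it content for one endpoint. For MI, a patient with a missing value is kept by imputation. For antibody level, nothing in the text keeps such a patient in.

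The model matters here because repeated measures ANCOVA, in its classical general linear model form, deletes a patient with any missing visit. One missed blood sample out of four would then remove the three that were taken. The antibody comparison would rest on patients who attended every visit, in a plan that says it analyses by intention-to-treat.

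Precision would be lost. The comparison could also be biased if attendance depends on arm or on the course of the disease. That is plausible: patients know whether they were operated on (only the examining ophthalmologist is masked, under Procedures for blinding and minimizing bias), and they may withdraw or be withdrawn at any time (Safety aspects).

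**Working it through.** **The plan's own figure.** The only stated calculation is the MI sample size under Power calculation: 29 per group, difference 0.7, SD 0.8, two-sided 0.05. The noncentral t distribution gives power 0.895 at 28 and 0.906 at 29 per group, so 29 for 90% reproduces. This point does not challenge it. The document gives no figure for missed visits.

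**Inputs.** N = 60 (Trial population). k = 4 post-randomization antibody values and k = 3 for the eye scores (Table 5). The missing rate per visit, m, is an assumption, shown from 2% to 15%.

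**Complete sets under independent misses.** The share with all k values is (1 − m)^k.

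| m | (1 − m)^4 | of 60 | (1 − m)^3 | of 60 |
|---|---|---|---|---|
| 2% | 0.922 | 55.3 | 0.941 | 56.5 |
| 5% | 0.815 | 48.9 | 0.857 | 51.4 |
| 10% | 0.656 | 39.4 | 0.729 | 43.7 |
| 15% | 0.522 | 31.3 | 0.614 | 36.8 |

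The three-visit columns matter only if CAScore or NOSPECS is analysed as continuous, which the document does not say.

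**Measurements discarded (antibody, 60 × 4 = 240 planned).**
- m = 5%: 240 × 0.95 = 228 observed; 4 × 48.9 ≈ 196 used; about 32 thrown away.
- m = 10%: 240 × 0.90 = 216 observed; 4 × 39.4 ≈ 157 used; about 59 thrown away.

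**Standard error relative to 60 complete patients.** This is 1/√share: 1/√0.815 = 1.11 at 5% and 1/√0.656 = 1.23 at 10%. A mixed model would recover part of this increase, not all of it, because the missed values stay missing.

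**If misses cluster.** At the other extreme the same patients miss every visit, and the complete share is 1 − m: 60 × 0.95 = 57 at 5% and 60 × 0.90 = 54 at 10%. Between independence and full clustering, the number remaining is therefore 49 to 57 at 5% and 39 to 54 at 10%.

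**Under a mixed model.** A patient with at least one post-randomization value stays in. With independent misses that share is 1 − m^k, above 99.6% at every rate shown, for three or four visits. With fully clustered misses the model gains nothing, because those patients have no follow-up value.

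**The case against.** A reader might infer that the plan excludes patients with a missed visit and that intention-to-treat therefore fails for these endpoints. The document does not support that. It names SPSS but no procedure, and SPSS can also fit a repeated measures model as a mixed model, which keeps partial data. No sentence excludes anyone. This part of the objection stands, and the loss is conditional on the classical fit.

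A second argument is that missing-data handling for endpoints other than MI is commonly left to the statistical analysis plan, which is announced here. As to silence alone, that is right. But the protocol article is not silent: it fixes the model, the contrast and the meaning of intention-to-treat. An analysis plan that follows it literally could adopt the classical form, which is the usual meaning of the phrase and fits a plan that keeps MI patients by imputing values. The article also treats analyses not mentioned in the protocol as explorative, so it is safer to name the mixed model there.

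Third, the same section says that secondary endpoints will be analysed at the time points in Tables 4 and 5. In separate by-visit analyses, one missed sample costs only that visit. This limits the harm for those analyses. It does not settle how the main contrast, the mean over all post-randomization measurements, is to be estimated.

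Fourth, the reach is narrow, and this stands. SNI and quality of life have one post-randomization value in Table 5, so the mechanism cannot touch them. The text under Post-treatment interventions, however, lists ultrasound at 16 and 32 weeks as well; if that schedule applied, SNI would come under the point. CAScore and NOSPECS are nowhere classed as continuous. The trial is powered on MI, which has its own missing-value rules.

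**Conclusion.** The point holds in conditional form, chiefly for antibody level. The plan gives intention-to-treat content for MI only, and it names a model that, fitted classically, would drop any patient missing one of four antibody samples. About 55, 49 or 39 of 60 would remain at 2%, 5% or 10% missing per visit. These rates and the independence of misses are assumptions; clustering raises the numbers, to at most 57 at 5% and 54 at 10%. Under a mixed model almost no patient with partial follow-up is lost.

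The MI sample size is unaffected. The case for change is that a better method than the one named is available at little cost.

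**What to change.** For antibody level, and for any eye score analysed as continuous at several visits, state that the model is a likelihood-based linear mixed model using all available visits, with:

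- group, visit (as a category) and group-by-visit as fixed effects;
- the endpoint's own baseline as covariate, and the stratification factor (MI grade II or III) as a factor, in place of baseline MI as the only covariate;
- unstructured covariance, with a fallback stated in advance (for example compound symmetry) if it does not converge;
- the same contrast as now, the group difference in the mean over all post-randomization visits, estimated from this model.

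Say that the analysis assumes values are missing at random, and report by arm how many patients have no post-randomization value, since the model cannot use them. Leave SNI and quality of life out of this change if each has a single post-randomization value as in Table 5.

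**Cost.** Wording in the protocol and the statistical analysis plan; no new data and no change of software. The downside is a few more covariance parameters with 60 patients: for four visits, 4 variances and 6 covariances, or 10, against 2 under compound symmetry.

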### Interventions

#### Pre-treatment interventions

At this screening visit, baseline data in the form of a case report will be documented, including past medical history, current medications, blood parameters, eye examination including slit-lamp bimicroscopy, indirect fundoscopy, visual acuity determination, Hertel exophthalmometry, ocular motility, CAScore and NOSPECS score as well as ocular ultrasound and quality of life questionnaire in German (see Additional file 1). Patients will then be randomized into one of the two treatment groups. All trial data will be collected and documented in the case report form (CRF) (see Additional file 2).

Tables 2 and 3 describe the muscle index (MI) and superonasal index (SNI).

**Table 2 Tab2:** Muscle index (MI)

Normal MI:	< 5.0	
Mild Graves’ orbitopathy	4.5–5.5	Grade I
Moderate Graves’ orbitopathy	5.5–6.5	Grade II
Severe Graves’ orbitopathy	> 6.5	Grade III

**Table 3 Tab3:** Superonasal index (SNI)

Normal SNI	< 5.75	
Danger for optic nerve compression	> 7.0	Grade IV

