**Fig. 2 Fig2:**
[figure not shown]
Study schedule

**Table 4 Tab4:** Pre-treatment schedule and parameters examined

	Initial screening until randomization						
	Day 1 (initial screening)	Day 2 (4–8 weeks after day 1)	Day 3 (4–8 weeks after day 2)	Day 4 (4–8 weeks after ATD reduction)	Day 5 (12–16 weeks after ATD reduction)	Day 6 (20–24 weeks after ATD reduction	
Pregnancy test	X	X	X	X	X	X	Randomization and treatment
Blood tests	X	X	X	X	X	X	
Slit-lamp bimicroscopy	X					X	
Indirect fundoscopy	X					X	
Visual acuity determination with Snellen test	X					X	
Hertel exophthalmometry	X					X	
Ocular motility, cover test, prism cover test, convergence	X					X	
CAScore/NOSPECS	X					X	
Ultrasound						X	
Adverse events		X	X	X	X	X	
Quality of life form	X						
Case report form	X	X	X	X	X	X	
Blood parameter form	X	X	X	X	X	X	
Current medication form	X	X	X	X	X	X	
Eye examination form	X					X	

Legend: *ATD* antithyroid drugs, *CAScore* Clinical Activity Score, *NOSPECS* No signs/symptoms, Only signs/no symptoms, Soft tissue involvement, Proptosis, Extraocular muscle involvement, Corneal involvement, Sight loss

**Table 5 Tab5:** Follow-up schedule and parameters examined

Follow-up schedule				
	Follow-up 1 (8 weeks following treatment)	Follow-up 2 (16 weeks following treatment)	Follow-up 3 (32 weeks following treatment)	Follow-up 4 (1 year following treatment)
Pregnancy test	X	X	X	X
Blood test	X	X	X	X
Slit-lamp bimicroscopy		X	X	X
Indirect fundoscopy		X	X	X
Visual acuity determination with Snellen test		X	X	X
Hertel exophthalmometry		X	X	X
Ocular motility, cover test, prism cover test, convergence		X	X	X
CAScore/NOSPECS		X	X	X
Ultrasound				X
Adverse events	X	X	X	X
Quality of life form				X
Case report form	X	X	X	X
Blood parameter form	X	X	X	X
Current medication form	X	X	X	X
Eye examination form		X	X	X

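### Antibody level, SNI, quality of life and the eye scores are adjusted for baseline MI but not for their own baselines, which costs efficiency (no bias, and no loss for MI itself)

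*Protocol article*

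**What the plan says.** **The model.** In the Protocol article, Statistical analysis, one method covers all of these endpoints: "The primary and continuous secondary endpoints will be analyzed using repeated measures analysis of covariance". The terms of that model are then fixed in the same sentence: "using the randomization group as factor and the baseline values of MI as covariate". No other covariate is named. The comparison is also fixed: "The contrast of main interest is the difference between groups in the means computed over all post-randomization measurements".

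**The endpoints.** The Objective of the study section names MI as a main outcome variable, "as well as thyroid antibody levels, measured at each follow-up appointment". CAScore/NOSPECS, SNI and quality of life are additional outcomes.

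**The baselines.** Table 4 ("Pre-treatment schedule and parameters examined") marks:
- blood tests at all six visits before randomisation;
- CAScore/NOSPECS at Day 1 and Day 6;
- ultrasound, the source of MI and SNI, at Day 6 only;
- the quality-of-life form at Day 1 only.

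The last visit before randomisation is "Day 6 (20–24 weeks after ATD reduction"). On quality of life the Statistical analysis section says only: "Quality of life questionnaire will also be obtained before randomization and after 1 year of follow-up".

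**Timing in the text.** Pre-treatment interventions lists ocular ultrasound and the questionnaire among the screening-visit assessments and continues: "Patients will then be randomized into one of the two treatment groups".

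**Stratification.** The Power calculation section stratifies randomisation by MI grade (II or III).

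**The concern.** The best single predictor of a continuous outcome is usually the same variable measured before randomisation. The plan uses that predictor for MI. For every other continuous endpoint it substitutes the baseline of a different variable, and there is no stated reason to expect an orbital ultrasound index to predict an antibody titre or a questionnaire score well.

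Two things are at stake for those endpoints. One is precision, which matters with 30 patients per arm. The other is protection against chance imbalance: if the arms happen to differ in baseline antibody level, adjustment for MI does not correct the antibody comparison. Antibody level is the most important case, because it is listed beside MI as a main outcome.

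The visit schedule adds a practical problem. If quality of life is to be adjusted for its own baseline, the only value on file comes from the first screening visit, months before randomisation.

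**Working it through.** **1. The plan's own figure, and whether it is affected.** Inputs from the Power calculation section: difference 0.7, SD of changes 0.8, two-sided alpha 0.05, power 90%, two-group t test. The normal approximation gives 28 per group. With the noncentral t distribution, power is 0.895 at 28 and 0.906 at 29, so the stated 29 reproduces. It concerns MI, whose covariate is its own baseline, so nothing below touches it.

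**2. Precision for the other endpoints.** After adjustment for one covariate with correlation r to the outcome, residual variance is proportional to 1 − r². Let r_own be the correlation of the endpoint with its own baseline and r_MI its correlation with baseline MI. The variance under the plan relative to own-baseline adjustment is

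(1 − r_MI²) / (1 − r_own²).

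The documents give neither correlation, so a range is assumed:

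| r_own | r_MI | Variance ratio | Effective N of 60 | Power if 80% with own baseline |
|---|---|---|---|---|
| 0.3 | 0 | 1/0.91 = 1.10 | 54.6 | 76% |
| 0.5 | 0 | 1/0.75 = 1.33 | 45.0 | 68% |
| 0.7 | 0 | 1/0.51 = 1.96 | 30.6 | 52% |
| 0.3 | 0.3 | 0.91/0.91 = 1.00 | 60.0 | 80% |
| 0.5 | 0.3 | 0.91/0.75 = 1.21 | 49.5 | 72% |
| 0.7 | 0.3 | 0.91/0.51 = 1.78 | 33.6 | 56% |

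The rows with r_MI = 0.3 allow for what the planned MI adjustment already achieves.

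**3. Antibody level averaged over four follow-ups.** Assume equal correlation ρ between all measurements and r_MI = 0. The mean of four has variance (1 + 3ρ)/4 and covariance ρ with baseline, so the ratio is [(1 + 3ρ)/4] / [(1 + 3ρ)/4 − ρ²].
- ρ = 0.3: 0.475/0.385 = 1.23
- ρ = 0.5: 0.625/0.375 = 1.67
- ρ = 0.7: 0.775/0.285 = 2.72

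Table 4 does not list the analytes in its blood tests; antibodies are taken to be among them.

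**4. Chance imbalance.** With 30 per arm, the standard error of a baseline difference is √(2/30) = 0.26 SD. A difference beyond 0.25 SD in either direction therefore occurs in about one trial in three for any given endpoint. Left uncorrected, at r_own 0.5 to 0.7 it shifts the estimate by 0.25 × 0.5 = 0.125 SD to 0.25 × 0.7 = 0.175 SD.

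**5. Age of the quality-of-life baseline.** No interval is stated. Summing the Table 4 windows:
- ATD reduction at Day 3: 4 + 4 + 20 = 28 to 8 + 8 + 24 = 40 weeks
- ATD reduction at Day 2: 4 + 20 = 24 to 8 + 24 = 32 weeks
- Visit order alone: Day 3 is at least 8 weeks after Day 1, and Day 6 at least 20 − 8 = 12 weeks after Day 4, so at least 20 weeks.

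If, as an example, the one-year score correlated at 0.7 with a Day 6 form but only 0.5 with the Day 1 form, adjusting for the older value would leave 0.75/0.51 = 1.47 times the variance.

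**6. Ultrasound timing.** Pre-treatment interventions places ultrasound at screening; Table 4 leaves Day 1 blank in that row and marks Day 6. Both cannot describe the same schedule.

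**The case against.** **MI is a defensible covariate.** Randomisation is stratified on MI grade, so MI or its grade belongs in the model. This stands, but it is a reason to keep MI, not to leave out the endpoint's own baseline.

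**The loss may be small.** The correlations are assumed. SNI is another orbital ultrasound index scheduled with MI, so MI may predict it fairly well. The eligibility limits on CAScore and SNI narrow the baseline range and could lower r_own. All of this stands, and the ratio falls to 1.00 when the two correlations are equal.

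**The unseen SAP or full protocol may settle it.** In general this is fair, but here the article does not leave the covariate open: it names one. It also says that analyses absent from the protocol will be treated as exploratory, so a silent change in the SAP would sit awkwardly with that rule.

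**Stronger readings the documents do not support.** A reader might infer any of the following:
- That the primary analysis or the sample size suffers. It does not (step 1).
- That the other comparisons are biased. Randomisation protects them; a chance imbalance adds error, not systematic error.
- That the early quality-of-life form itself loses precision under the plan. In the stated model that baseline is not used. Its age matters only once it enters as a covariate or a change score is analysed, and even then it adds noise, because the course before randomisation is common to both arms.
- That the gap is fixed at 28 to 40 weeks, or that the form precedes the glucocorticoid course. The first depends on when ATD is reduced. For the second, Table 4 does not show the course at all.

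**The ultrasound conflict may be compressed prose.** Other sections place MI before randomisation, and the Kahaly scheme section randomises on relapse after 4 to 6 months, which fits Table 4 better. The passages still differ.

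**Conclusion.** The point holds for the continuous endpoints other than MI. As written, antibody level, SNI, quality of life, and CAScore/NOSPECS where treated as continuous forgo adjustment for baselines that the trial collects. With own-baseline correlations of 0.5 to 0.7, the treatment-effect variance is inflated by a factor of 1.33 to 1.96 if MI carries no information and 1.21 to 1.78 if MI correlates at 0.3; the factor is 1 if MI does as well as the own baseline. These figures rest entirely on assumed correlations.

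This is a matter of efficiency and of protection against chance imbalance, not of validity. The single early quality-of-life form limits how much the remedy can achieve for that endpoint. The disagreement over ultrasound timing is a separate clarification, worth making because that scan supplies the MI covariate and the stratification grade.

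**What to change.** 1. In Statistical analysis, state that each continuous endpoint is adjusted for its own last value before randomisation, with baseline MI or MI grade as a second covariate because it is the stratification factor. For MI the first covariate is baseline MI, as now. This costs one sentence and one residual degree of freedom per added covariate.
2. Add the quality-of-life form at Day 6 in Table 4 and use that value as its baseline. This costs one more questionnaire at a visit patients already attend.
3. Reconcile Pre-treatment interventions with Table 4 on the ultrasound, so that the MI and SNI baseline is the value obtained just before randomisation. This is an edit to the text only.

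Changes 1 and 3 can be made without new data. Change 2 helps only patients not yet past Day 6. For any others the Day 1 value is the only baseline, and the report should say so.
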